##### Measures

To meet the study objectives, the questionnaire will consist of the following sections: (1) sociodemographic characteristics and (2) the level of acceptability of a PBD to treat hypertension among farmers. The sociodemographic characteristics will include age, gender, marital status, education (no formal education, elementary school, middle school, and high school or higher), household monthly income per capita (less than US $65.82, US $65.82-131.65, US $131.66-197.47, and over US $197.47), duration of hypertension (years), grade of hypertension based on the JNC VIII criteria, and living condition (with children or a spouse). In section 2 of the questionnaire, a 4-point Likert scale will be used to assess the level of acceptability of a PBD to treat hypertension among farmers. Expectations will be measured as follows: 1, strongly disagree; 2, disagree; 3, agree; and 4, strongly agree. A higher score will indicate a higher level of acceptability of a PBD to treat hypertension among farmers. The association of sociodemographic factors with the different categories of expectations and acceptability will be determined through statistical analysis.

##### Sampling Process

Representative research respondents will be selected by collecting available data on public health services. Farmers with hypertension are listed as regular patients in the Posbindu PTM (Pos Pembinaan Terpadu Penyakit Tidak Menular) program of the public health services. The data obtained will be assessed in a random process to select respondents using a simple random sampling technique. We will use a randomizer application that is available online to select respondents. Respondents selected from the randomizer application will then be included in the list of research respondents. We will follow the activities of the Posbindu PTM program as well as meet with research respondents who have been selected to be able to collect research data. We will print out the questionnaire and give it to the research respondents to fill out. Our team will assist farmers in filling out questionnaires to ensure that the questionnaires given are filled out completely and accurately.

##### Analysis Plan

The data from the questionnaire will be inputted into SPSS (IBM Corp) for analysis. We will perform data cleaning to check each data point from the questionnaire and ensure there are no missing data from the entire questionnaire. We will only use completed questionnaires for analysis. After the data cleaning process is complete, we will perform the data analysis process.

We will use descriptive statistics to describe the characteristics of the respondents and the level of acceptability of a PBD to treat hypertension among farmers according to data distribution. Numerical variables will be shown as means and standard deviations or medians and interquartile ranges, while categorical variables will be shown as absolute frequencies and percentages. We will use the chi-square test to examine the sociodemographic factors associated with farmers’ different categories of acceptability. With the 95% CI, a *P* value of <.05 will be considered statistically significant.

We will use multiple logistic regression models to estimate the associated and independent factors from the sociodemographic factors and the level of acceptability of a PBD among farmers. In the case of a low event rate and low sample size for expectations and acceptability in the definite form, we may recode them into tertiles and use the lowest score category as the reference group. Alternatively, we may conduct multiple linear regression analyses with the 2 dependent variables as continuous variables. We will also include any independent factors with a *P* value <.20 from the univariable regression analysis in the multiple regression analysis. Multicollinearity between independent variables will be checked according to a tolerance value <0.4 (variance inflation factor ≥2.5). In the presence of multicollinearity, we will select the more critical or essential variables from clinical perspectives for use in the final regression analysis. We will check all models, check Q-Q plots for normality, check residual plots for linearity, and check homogeneity assumptions, as well as assess model fitting.

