**Conclusions:**

The PBD model will not be readily available for other agricultural areas since validation of local food variation is required to design the menu. We expect contributions from the local government to implement the intervention as one of the policies in the management of hypertension for farmers in the agricultural plantation areas of Jember. This program may also be implemented in other agricultural countries with similar problems, so that hypertension can be optimally treated among farmers.

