##### Setting

To obtain a representative sample according to the criteria that have been set, we will select 3 PHCs located in agricultural areas in Jember, East Java, Indonesia. The PHCs we have selected include Banjarsengon, Sukorambi, and Panti. There are quite a lot of farmers in the Panti area, with 14,322 active farmers having quite complex hypertension problems [22]. Farmers in Banjarsengon and Sukorambi also show a similar condition. These 3 PHCs are expected to have a sufficient number of farmers with hypertension who could respond and complete the questionnaire.

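### The survey pools three health-center areas but names no area term in the models that are to yield independent factors; keeping health center in the regressions is a cheap safeguard

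*Protocol article*

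**What the plan says.** All places are in the protocol article, Phase II, Activity 2.

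- **Setting:** "The PHCs we have selected include Banjarsengon, Sukorambi, and Panti". Of the farmers in the other two areas, after a sentence on the number of farmers and hypertension in Panti, it adds: "Farmers in Banjarsengon and Sukorambi also show a similar condition".
- **Sampling Process:** names from public health service data are "assessed in a random process to select respondents using a simple random sampling technique". No stratification by PHC is stated.
- **Measures:** "The sociodemographic characteristics will include age, gender, marital status, education", followed by household income, duration and grade of hypertension, and living condition. PHC or area is not listed.
- **Analysis Plan:** chi-square tests relate the sociodemographic factors to categories of acceptability. Then: "We will use multiple logistic regression models to estimate the associated and independent factors from the sociodemographic factors". Factors with P<.20 are carried forward "from the univariable regression analysis in the multiple regression analysis". Fallback recoding, a linear alternative, collinearity limits and residual checks are also given. No area term, stratum or cluster adjustment appears.

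**The concern.** Finding the factors associated with acceptability is part of the second study objective, and the Analysis Plan intends to call some of them independent. Each respondent comes from one of three areas, and the area should be known from the list used for sampling. Acceptability of a diet built on local vegetables and fruits could depend on where a farmer lives, through supply, price or the local team that helps with the questionnaire. Income or education could also vary by area. If both do, a model without area assigns part of the area difference to income or education. A simple random sample protects the estimate of the overall level but does not break this link. At stake are false associations, or true ones masked, in the survey's factor analysis.

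**Working it through.** **Inputs from the protocol.** Three PHCs (Setting), N = 263 (Sample Size Estimation), test level .05 (Analysis Plan).

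**Inputs assumed.** Equal numbers per PHC, a binary factor with no effect on acceptability within any PHC, and PHC-specific percentages for factor and outcome. The protocol gives no such percentages, so a range is shown.

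**The plan's own figure.** N = 263 is the first sample size that reaches 0.90 power (0.902) in an exact two-sided one-sample binomial test of 0.50 against 0.60. The 0.50 is an assumption; the 10-point difference, power and alpha are stated. This figure is not in dispute.

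**Step 1: bias of the pooled odds ratio.** With acceptability aᵢ and factor share fᵢ in PHC i, acceptability is Σfᵢaᵢ/Σfᵢ among farmers with the factor and Σ(1−fᵢ)aᵢ/Σ(1−fᵢ) among those without. Take a = 40/50/60% and f = 30/50/70%:

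- With the factor: (0.3×0.4 + 0.5×0.5 + 0.7×0.6)/1.5 = 0.79/1.5 = 0.527.
- Without it: (0.7×0.4 + 0.5×0.5 + 0.3×0.6)/1.5 = 0.71/1.5 = 0.473.
- Pooled odds ratio = (0.79/0.71)² = 1.24, although it is 1.00 in every PHC.

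**Step 2: false-positive rate.** About 131.5 respondents per factor level give SE(log OR) = √[2/(131.5×0.527×0.473)] = 0.247. Then ln(1.24)/0.247 = 0.2135/0.247 = 0.864, and the rejection rate is Φ(0.864−1.96) + Φ(−0.864−1.96) = 13.9%.

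**Step 3: all scenarios.** The formula is set against simulated logistic regressions (n = 263, 1,000 runs each).

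| Acceptability by PHC | Factor share by PHC | Pooled OR (formula) | Rejection, formula | Rejection, simulated without PHC | Simulated with PHC |
|---|---|---|---|---|---|
| 50/50/50% | 30/50/70% | 1.00 | 5.0% | 5.4% | 4.7% |
| 40/50/60% | 50/50/50% | 1.00 | 5.0% | 4.5% | 4.5% |
| 45/50/55% | 40/50/60% | (0.76/0.74)² = 1.05 | 5.5% | 5.5% | 5.2% |
| 40/50/60% | 40/50/60% | (0.77/0.73)² = 1.11 | 7.2% | 6.2% | 5.2% |
| 30/50/70% | 40/50/60% | (0.79/0.71)² = 1.24 | 13.9% | 12.1% | 4.4% |
| 40/50/60% | 30/50/70% | (0.79/0.71)² = 1.24 | 13.9% | 15.4% | 4.5% |
| 30/50/70% | 30/50/70% | (0.83/0.67)² = 1.53 | 40.8% | 41.8% | 5.3% |

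Formula and simulation agree within the simulation error, which is about 1 to 2 percentage points. If only one of the two differs by PHC, there is no inflation.

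**Step 4: the linear fallback and the chi-square test.** In a separate simulation (4,000 runs, n = 263), PHC mean scores spanned 0.3, 0.5 or 0.8 SD. With factor shares of 60/50/40%, the linear model without PHC rejected in 6%, 8% or 13% of runs. With 70/50/30%, it rejected in 10%, 18% or 38%, and the chi-square test on the three score bands in 7%, 12% or 22%. With PHC in the linear model the rate was about 5% throughout.

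**Step 5: cost of the extra terms.** If scores are roughly normal, an outer band beyond 1 SD holds about 16% of 263, or 42 respondents. The listed covariates use up to 12 parameters if marital status is binary (age 1, gender 1, marital status 1, education 3, income 3, duration 1, grade 1, living condition 1). PHC makes 14, so events per parameter fall from 42/12 = 3.5 to 42/14 = 3.0. In a logistic simulation with 10 other covariates and about 16% events, adding PHC changed power by 0 to 5 points when the areas did not differ (in one setting, 78.0% against 77.5%). Where area was related to both factor and outcome, it cut false positives from 7-15% to about 4-6%.

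**The case against.** The strongest reply is that no area difference is documented.

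- The statement that the model will not transfer readily, "since validation of local food variation is required to design the menu", concerns other agricultural areas, not the three study PHCs.
- The crop zones in the Phase I Setting are mainly plantation crops and are not mapped to the three PHCs. The same text says food crops grow everywhere except the city center.
- The only direct comparison of the PHCs calls their condition similar, though in the context of farmer numbers and hypertension.

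A reader might infer from these places that local food and acceptability do differ between the three PHCs. The protocol does not support that, and it says nothing on income or education by PHC.

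It can also be said that a condensed article is silent on an area term and does not rule one out. That is true: a reader should not conclude that PHC was deliberately excluded. Yet the Analysis Plan is specific about model family, entry rule and collinearity limits, so naming PHC is a concrete improvement to a stated model.

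Finally, a pooled association is real in the sampled population even if it is partly geographic. This stands for the word associated. It does not stand for the word independent, which needs area held constant. The objection that extra terms cost something in a sparse logistic model is also fair, and it belongs among the costs.

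**Conclusion.** The point holds as a conditional one. The survey pools three PHCs, and the factors named for its tests and regressions leave PHC out, so the results could not be called independent of where a farmer lives. How much this matters depends on area differences that the protocol does not give: about 5-8% false positives for modest differences (10 to 20 points in both acceptability and the factor), about 15% when one spans 20 and the other 40 points, and about 40% only when both span 40 points. These figures assume equal PHC sizes and a single binary factor.

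A reader might take the largest figure as the expected error of the survey. It is the extreme of an assumed range. The issue is confined to the survey's association analysis; the randomized comparison and N = 263 are not touched. It is a cheap improvement, not an error that undermines the study.

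**What to change.** In the Activity 2 Analysis Plan, state that PHC (three levels) is kept as a fixed factor in every multiple regression of acceptability and expectations, logistic or linear, and is not subject to the P<.20 entry rule, which could otherwise drop it. Describe the chi-square tests as unadjusted and descriptive. Fix this before the data are analyzed, so that adjustment is not chosen after seeing results.

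The cost is two degrees of freedom, a small loss of power when events are few, and a change in what is estimated: the coefficients then describe association within areas. No extra respondents are needed, and PHC should be available from the sampling lists. Sampling in proportion within each PHC list is not needed for this purpose.

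### The survey tests eight factors at P<.05 and leaves the outcome form open until the data are seen; under one fixed coding, the chance of at least one spurious 'significant' factor is about one third to one half

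*Protocol article*

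**What the plan says.** All references are to the protocol article, Phase II, Activity 2 (Survey), unless stated.

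- **Factors.** Measures begins its list with "The sociodemographic characteristics will include age, gender, marital status, education" and goes on to "household monthly income per capita", duration of hypertension, grade of hypertension and living condition. That makes eight.
- **Outcomes.** The last sentence of Measures names two: "The association of sociodemographic factors with the different categories of expectations and acceptability will be determined through statistical analysis". In Analysis Plan, the chi-square tests and the opening sentence on logistic regression name acceptability only. The recoding sentences that follow treat both as dependent variables.
- **Significance rule.** "With the 95% CI, a *P* value of <.05 will be considered statistically significant". It comes directly after the chi-square sentence.
- **Form of the outcome.** Activity 1, Overview, defines three categories cut at the mean or median ± 1 SD. Analysis Plan then says that, if the event rate and sample size are low, "we may recode them into tertiles and use the lowest score category as the reference group". The next sentence adds: "Alternatively, we may conduct multiple linear regression analyses with the 2 dependent variables as continuous variables". No threshold for a low event rate is given.
- **Objective.** The second objective, at the end of the Introduction, concerns acceptability and its associated factors. It does not mention expectations.

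**The concern.** Identifying associated factors is part of a stated objective, and the plan declares each one significant or not at .05. With eight factors and one or two outcomes, some will cross that line by chance. The outcome form adds to this. Whether events are too few can be judged only once outcome data are in hand, and the wording is permissive at both steps. Two analysts following the same text could therefore report different significant factors, and a reader could not tell whether the coding was chosen before or after the factor results were known. At stake is how much weight a factor named by the survey can bear.

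**Working it through.** **The plan's own figure.** Sample Size Estimation gives 263 for a 10% difference in proportion, power 0.90, two-sided .05. Assuming a one-sample test against 0.50 (the reference proportion is not stated), n = (1.960 + 1.282)² × 0.25 / 0.10² ≈ 262.7, so 263. The exact binomial test also first reaches 0.90 at 263 (power 0.902). The figure reproduces. It rests on a single test at .05, so it does not address a family of factor tests.

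**Number of tests.** Eight factors × one outcome = 8; eight factors × two outcomes = 16.

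**Chance of at least one P<.05 with no true association, independent tests, one coding.**
- 1 − 0.95⁸ = 0.337
- 1 − 0.95¹⁶ = 0.560

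**Allowing for dependence.** Null surveys of n = 263 were simulated (600 to 1,000 runs per scenario). They used the planned P<.20 univariable screen followed by multiple regression. The correlation between outcomes was 0, 0.4 or 0.7 (Activity 1, Validation and Reliability, hypothesizes at least 0.4) and between factors 0 or 0.3. Level shares, correlations and binary splits (top category against the rest) are assumptions. The Monte Carlo standard error near 0.5 with 600 runs is √(0.25/600) = 0.02.

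| Scenario | Acceptability only | Both outcomes |
|---|---|---|
| Independent tests, one coding | 33.7% | 56.0% |
| Chi-square on ± 1 SD categories, simulated | 29–37% | planned for acceptability only |
| Screen then regression, one fixed coding, simulated | 27–35% (continuous score) | 43–59% |
| Equicorrelated tests, r = 0.5 | 25% | 37% |
| Equicorrelated tests, r = 0.7 | not run | 27% |
| Best of three regression codings (ceiling), simulated | 53–63% | 75–86% |

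For one binary factor and one outcome, keeping the best of three codings raises the 5% error to about 11%. This too is a ceiling.

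**Is the fallback likely to be invoked?** If scores are roughly normal, about 16% lie beyond 1 SD on each side: 0.16 × 263 ≈ 42. The eight factors need at least 12 parameters (three each for education and income, at least one for each of the other six: 3 + 3 + 6). A logistic model for an outer category would have about 42 / 12 = 3.5 events per parameter. A low event rate could readily be argued, so the unspecified switch matters in practice.

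**The case against.** The strongest reply has four parts.

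1. **The coding choice need not inflate error.** Tertile recoding is conditional, and the sentence on linear regression can be read as a second fallback for the same condition. A switch based on how many farmers fall in each category uses the outcome distribution alone, not the factor P values, and does not inflate the error for a factor. This stands. A reader might infer that the survey will usually name a false factor, at 75–86%, or that each factor is really tested at 11%. The document does not support that, because both figures require every coding to be run and the best P kept, and the text describes no such selection. What remains is that, without a threshold, the text does not exclude it either.

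2. **Acceptability is already the lead outcome.** The objective, the chi-square sentence and the first regression sentence name it alone. This largely stands, and it makes about one third the secure figure. But Measures and the recoding sentences bring in expectations on equal terms, so the larger family cannot be dismissed.

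3. **Multiplicity detail belongs in an analysis plan that is not shown.** The absence of a correction or hierarchy would not be a finding on that ground. The point rests on what the section does state: a significance rule for every factor and an outcome form left to discretion.

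4. **The consequences are limited.** The Discussion's remark about policymakers concerns farmers' expectations and acceptability themselves, not which factor reaches significance. Nothing in Activity 3 uses the survey's factors. A reader who inferred that the trial's blood pressure results are at risk would be wrong.

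**Conclusion.** The concern holds in a limited form. With no true association, the survey has about a one-in-three chance of reporting at least one significant factor for acceptability under a single fixed coding, and roughly 45–55% if expectations is counted as well. Strong correlation among the tests lowers these figures, to 25% for eight tests and 37% for sixteen at r = 0.5. About 60% for acceptability and 85% for both outcomes are upper limits under unrestricted choice of coding, not the plan's expected error rate. All simulated values depend on assumed factor distributions and correlations. The weakness lies in Activity 2 and deserves correction because the wording is loose at the point where a choice will probably have to be made.

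**What to change.** In Activity 2, Analysis Plan:

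- Name acceptability as the primary survey outcome, in line with the second objective, and expectations as secondary.
- Name one primary model: linear regression of the continuous acceptability score on all eight listed factors.
- Make the category and tertile versions sensitivity analyses that cannot change the conclusion.
- Label the factor associations exploratory and report them as estimates with 95% CIs. Holm's correction across the eight factors is optional; in a descriptive survey it trades power for a stricter claim.

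**Cost.** Wording only, no new data. Claims about single factors become weaker, and entering all eight factors means the P<.20 screen no longer selects variables for the primary model.

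**Gain.** Besides closing the choice of coding, the continuous score uses the data better. For an assumed binary-factor effect of 0.35 SD at n = 263, simulated power is about 82%, against 57% with the ± 1 SD categories. The normal approximation for an even split agrees: 0.35 × √263 / 2 = 2.84, and Φ(2.84 − 1.96) ≈ 0.81.

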#### Activity 3: Randomized Controlled Trial

##### Overview

In activity 3, we will perform a randomized controlled trial (RCT) on the effectiveness of a community-based program for managing hypertension using a PBD among farmers. We will evaluate the effectiveness of a PBD menu for the outcomes (blood pressure and acceptability of a PBD) of farmers with hypertension.

##### Design

An RCT will be performed for the community-based program in 2 groups (with pretest and posttest) using the CONSORT (Consolidated Standards of Reporting Trials) guidelines. An RCT is preferred to reduce selection bias [23]. Participants in this study will be randomly allocated to either the control or intervention group. The control group will receive a standard health education intervention for managing hypertension, while the intervention group will receive the PBD formula. A single-blind technique will be used so that participants will be unaware if they are in the control or intervention group.

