##### Randomization

Initially, public health nurses (PHNs) will visit the study areas and make announcements about the study for farmer participation. The recruitment will be open for 6 months. Farmers will visit the PHC and will be provided an explanation of the study. Informed consent will be obtained, and farmers will be randomized using a computer-generated number. The allocation sequence will be concealed from the researchers and farmers. The computer-generated number system will randomize the initial name of the farmers from the PHC. The PHNs from the PHC will then obtain informed consent and manage the study groups.

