##### Outcome Measures

The main outcome measures in this study are SBP and DBP, which will be measured using a standard protocol employing a stethoscope and sphygmomanometer after stabilizing subjects for more than 10 minutes. Measurements of SBP and DBP (mmHg) will be categorized according to the JNC VIII criteria to determine hypertension for participants aged >18 years [24]. The length of work per day, time of rest during working, and hours of sleep per day will be assessed among the farmers. These factors will be measured as they can influence blood pressure among farmers, according to a previous study [2]. Manual blood pressure measurement is usually performed using a mercury device or a calibrated needle (aneroid). SBP and DBP are determined through auscultation by listening for the appearance and disappearance of Korotkoff sounds in the brachial artery. Blood pressure measurements will be taken after a 14-minute rest period, during which the researcher and the participant will have a conversation to reduce tension associated with the “white coat” effect. Measurements will be taken at the same time (ie, 8 AM before activities) with the same tool. Participants will be told not to wear clothes that are too thick. Blood pressure test results will be more accurate if the cuff is placed directly over the skin. Participants will be told to empty their bladder before measurement. For the measurement, participants will be told to sit with their arms on a table so that the elbows are in line with the heart, the back is well supported by the back of the chair, and the feet are on the floor.

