##### Data Collection Plan

At baseline, sociodemographic data, including age, gender, education level, smoking, hours of work, rest during working, and hours of sleep per day, will be obtained using a self-administered questionnaire. For measuring SBP and DBP at the PHC, participants will sit in a chair and relax for 10 minutes. Then, PHNs will measure blood pressure at least twice. If the blood pressure values obtained in the second measurement differ from the values in the first measurement by ≥10 mmHg, a third measurement will be carried out. The 2 measurement values with the smallest difference will be averaged to obtain the final value [24].

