##### Control Group Arm

The control group will receive a standard education intervention through the IHC for NCDs and available health services that can be accessed every month in the community.

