##### Intervention

The intervention group will receive a PBD formulated by the researchers. Farmers will consume the plant-based food 3 times per week. For the PBD, we will adopt a standard protocol from previous studies [1]. Therefore, we have decided to provide the PBD for 6 months.

In the control group, participants will receive education on health and safety on attending the IHP for NCDs, and they will adopt healthy behaviors according to the health education. As they will receive health education, they will be able to lead a healthy life in the agricultural environment, with occupational health and safety.

In both study groups, health education will be provided before the program, which will include information on how to manage a healthy lifestyle while working as farmers, including diet, exercise, rest, and sleep, and how to address blood pressure problems among farmers. Participants will receive this health education in a single session for 60 minutes at the first screening meeting. All participants will receive a manual book on a healthy lifestyle in an agricultural setting.

The blood pressure of participants in both study groups will be maintained. If the blood pressure increases to hypertension stage II or above, appropriate treatment will be provided by the medical doctor in the PHC and the participant will be excluded from the study. Data will be obtained at registration and at the pretest and posttest assessments. For blood pressure data, we will use rounded values, with values ending in 0-4 being rounded to “0” and values ending in 6-10 being rounded to “10” (eg, 120-124 mmHg will be rounded to 120 mmHg, 125 mmHg will be used directly, and 126-130 mmHg will be rounded to 130 mmHg).

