### Ethical Considerations

This study has received ethical approval from the Ethics Committee for Research Involving Human Subjects, Faculty of Dentistry of Universitas Jember (approval number: 1548/UN25.8/KEPK/DL/2022, with an amendment on June 29, 2021) and conforms to the requirements of the World Medical Association’s Declaration of Helsinki. All the participants will provide written informed consent before their inclusion.

This study will use descriptive analytics in health and community service units with a quantitative approach through surveys and qualitative interviews at health and community service units. This research will not cause harm to the participants. Each participant will provide informed consent. We will give autonomy rights to prospective participants. Participants will be provided an explanation of the study, including the objectives, benefits, implementation process, and participant rights. Participants will be informed that there is no risk of harm if they do not participate in the study or leave the study while the research process is in progress.

The study will pay attention to safety aspects for both the researchers and participants, and will be performed according to the applicable COVID-19 protocol. The interviews will be adjusted according to the participants’ time. Participants will receive compensation (transportation fee) and food for each data collection. The design of this study involves an intervention group and a control group, and we will try to minimize the occurrence of unwanted incidents during the implementation of the intervention. We will provide leaflets containing educational materials for a PBD when the last measurement is taken. Participants in the control group will be offered a discussion session after reading the leaflet provided, but there is no compulsion to join the discussion session. All participants in the intervention group will receive the same intervention regardless of ethnicity, religion, and race.

The confidentiality of the participants’ data will be maintained, and the identity of the participants will not be disclosed. The data obtained will only be used for research purposes. To keep participants’ data confidential, the survey sheet will have a special code that does not display the personal data. Moreover, a statement will be provided that qualitative study data are anonymous or deidentified. Furthermore, a brief description of the protections in place will be provided.

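### Participants cannot be kept unaware of their arm as described, no assessor blinding is stated for the manual blood pressure outcome, and the order of consent and randomisation is contradictory

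*Protocol article*

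**What the plan says.** **Blinding.** The Design section of Activity 3 claims blinding for participants only: "A single-blind technique will be used so that participants will be unaware if they are in the control or intervention group".

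**Arms.** Under Intervention, the active arm receives a diet formulated by the researchers: "Farmers will consume the plant-based food 3 times per week". The section Control Group Arm describes the comparator: "The control group will receive a standard education intervention through the IHC for NCDs and available health services that can be accessed every month". Both arms also get one shared education session and a manual. No control or sham food is described.

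**Information to participants.** Ethical Considerations says: "Participants will be provided an explanation of the study, including the objectives, benefits, implementation process, and participant rights".

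**Outcome assessment.** Outcome Measures makes systolic and diastolic pressure the main outcomes, measured manually: "SBP and DBP are determined through auscultation by listening for the appearance and disappearance of Korotkoff sounds". Data Collection Plan names the measurers: "Then, PHNs will measure blood pressure at least twice".

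**Consent and allocation.** Randomization first says: "Informed consent will be obtained, and farmers will be randomized using a computer-generated number". It then says that the sequence is hidden from researchers and farmers, describes the computer randomising the names, and ends: "The PHNs from the PHC will then obtain informed consent and manage the study groups". Ethical Considerations places written consent ahead of inclusion.

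**The concern.** A report that repeats the single-blind statement would claim a protection the trial does not have. Participants who eat a provided menu for months know what they are receiving. Besides blood pressure, the Activity 3 overview lists acceptability of the diet as an outcome. Acceptability is self-reported, so it is directly exposed to that knowledge.

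The main outcome depends on a person listening through a stethoscope and deciding when sounds appear and disappear. If that person knows the arm, readings can drift in the expected direction, and no analysis can remove the drift afterwards. The blood pressure reading also determines removal from the study when it reaches stage II or above, so the exposure extends to who remains in the trial.

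The order of consent matters separately. If a nurse who knows the allocation seeks consent, who enters each arm can depend on the allocation, and the arms are no longer comparable by design.

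**Working it through.** No arithmetic settles this point, and the plan gives no figure for it. The check is to set the statements side by side.

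**1. Can participants be unaware of their arm?**
- Intervention arm: researcher-formulated plant-based food, provided for 6 months and eaten 3 times per week (Intervention).
- Control arm: education through the health centre programme and the usual monthly services (Control Group Arm).
- Masking device: none described. The shared education session and manual are the same in both arms, but the food is not.
- Monitoring: the limitations section calls for a diary to track the diet.
- Result: a participant in the intervention arm cannot miss the food. The Design statement covers both arms, so it already fails for one. In the control arm, awareness depends on how much of the implementation process is explained.

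**2. Is the outcome assessor protected?**
- Scope of the claim: the Design section defines single-blind by reference to participants. No section says that blood pressure is read by someone unaware of the arm.
- Who manages the groups: public health nurses (Randomization).
- Who measures: public health nurses (Data Collection Plan).
- How: manual auscultation (Outcome Measures), preceded by a rest period in which the researcher and participant talk. The study diet can easily come up then.
- Stated safeguards: fixed time, posture and tool; at least two readings; a third if they differ by 10 mmHg or more; the two closest averaged; interrater checks and calibration.
- Result: the safeguards reduce random error and differences between observers or devices. They do not stop a shift that follows the arm, because an observer who knows the arm can be consistent across repeat readings and use a calibrated device.

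**3. Which comes first, consent or randomisation?**

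| Place | Order given |
|---|---|
| Randomization, early sentence | Consent, then randomisation |
| Randomization, last sentence | Names randomised, then consent by the nurses |
| Ethical Considerations | Consent before inclusion |

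Two statements point to consent first and one to consent second. Selection bias needs two conditions together: the last sentence describes what happens, and the nurse knows the allocation at that moment. The document establishes neither, and the stated concealment of the sequence speaks against the second.

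**The case against.** **Consent.** A reader might infer that consent is taken after randomisation by nurses who know the arm, so that concealment is lost. The document does not support that as fact. The same section also gives the opposite order, Ethical Considerations agrees with consent first, and the final sentence may only restate who takes consent. The section also says that the sequence is concealed. No mechanism is described, but a condensed article commonly leaves that out. What stands is a contradiction to be reconciled.

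**Nurses.** A reader might also infer that the same individual nurses run an arm and measure its participants. The text names a role across three health centres, and the limitations section speaks of different enumerators. What stands is that nothing separates the two tasks and no assessor blinding is stated.

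**Participants.** The ethics text does not say that the content of both arms is disclosed, and leaflets on the diet are held back until the last measurement. The intention may be that controls do not know what the other arm receives. That could partly mask the controls, but it does not rescue a claim that also covers people eating the food.

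**Measurement.** The procedure is well standardised, which limits the observer's latitude. It does not deal with knowledge of the arm.

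**Size.** It is tempting to express a reading bias as a share of the difference the trial can detect. The document gives no standard deviation for blood pressure and no allocation ratio. Its sample size of 96 comes from a McNemar calculation, not from a comparison of mean pressures. Any such percentage would rest on assumed values, so none is offered.

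**Conclusion.** The point holds in three parts of different strength:

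- **Participant blinding** is wrong as written. This follows from the description of the arms alone.
- **Assessor blinding** is not stated for an observer-dependent main outcome, and one staff role both manages the groups and measures. Observer bias is therefore possible. It is not shown to occur, since the document does not say that the same individuals do both tasks.
- **Consent order** is internally inconsistent. Selection bias is conditional on the second order being followed by a nurse who knows the allocation.

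The magnitude cannot be estimated from the document. The sample size is not affected. The first and third parts are faults of wording that must be corrected before the trial is reported. The second needs an operational decision before measurement begins, because it cannot be repaired at analysis.

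**What to change.** 1. **Design:** replace the single-blind sentence with a statement that the trial is open-label for participants. Cost: rewording only.
2. **Randomization:** state one order, namely consent, pretest blood pressure, then allocation revealed. Delete the second consent step. Cost: rewording only.
3. **Data Collection Plan:** among the existing public health nurses, have both pretest and posttest blood pressure taken by nurses who do not manage that participant's group and who see only the study code. Using such nurses at both time points avoids adding a change of observer between pretest and posttest, which is the enumerator variation the limitations section wants to keep down.
4. **Outcome Measures:** keep the conversation before measurement away from the study diet. Participants may still reveal their arm, so the masking will be imperfect.
5. **Fallback:** if staffing does not allow the separation, report the blood pressure outcome as unblinded.

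The cost of item 3 is some rota changes or travel between centres. The number of nurses is not given, and measurement is fixed at 8 AM, so whether existing staff suffice cannot be confirmed from the document. Hence the fallback.
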